## Abstract

**Background:**

Grieving relatives can suffer from numerous consequences like anxiety, depression, post-traumatic stress disorder (PTSD) symptoms, and prolonged grief. This study aims to assess the psychological consequences of grieving relatives after patients’ death in French palliative care units and their needs for support.

**Methods:**

This is a prospective observational multicenter mixed study. Relatives of adult patients with a neoplasia expected to be hospitalized more than 72 h in a palliative care unit for end-of-life issues will be included within 48 h after patient admission. End-of-life issues are defined by the physician at patient admission. Relatives who are not able to have a phone call at 6-months are excluded. The primary outcome is the incidence of prolonged grief reaction defined by an ICG (Inventory Complicate Grief) > 25 (0 best-76 worst) at 6 months after patient’ death. Prespecified secondary outcomes are the risk factors of prolonged grief, anxiety and depression symptoms between day 3 and day 5 and at 6 months after patients’ death based on an Hospital Anxiety and Depression score (range 0–42) > 8 for each subscale (minimal clinically important difference: 2.5), post-traumatic stress disorder symptoms 6 months after patient’ death based on the Impact of Events Scale questionnaire (0 best-88 worst) score > 22, experience of relatives during palliative care based on the Fami-Life questionnaire, specifically built for the study. Between 6 and 12 months after the patient’s death, a phone interview with relatives with prolonged grief reactions will be planned by a psychologist to understand the complex system of grief. It will be analyzed with the Interpretative Phenomenological Analysis. We planned to enroll 500 patients and their close relatives assuming a 25% prolonged grief rate and a 6-month follow-up available in 60% of relatives.

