##### Patient’s characteristics

The following data will be collected: demographic characteristics, diagnosis and localization of the neoplasia, presence of metastases, diagnosis of comorbid conditions, symptoms present on admission, presence of advances directives and of a surrogate, patient’s status at discharge, and length of stay. Request of euthanasia at admission or during the stay by patient and use of a continuous sedation until death will be collected.

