#### Organization of the study

In each center, a local team (physician and nurse or psychologist) will conduct the study. Consecutive patients will be approached within the first 48 h after palliative care admission. Examination of eligibility, its confirmation and inclusion will be performed by the local team. If the relative agrees, the patient will be invited to participate in the study giving permission of using his/her baseline medical information. After inclusion, between day 3 and day 5 after patient admission, a HADS questionnaire [19] will be administered to each relative included in the study.

At 6 months after the patient’s death, the psychologist will call the included relatives to fulfil the questionnaires in a random order (HADS [19], PTSD [20], IGC [21, 22]. The Fami-Life questionnaire, specifically built for the study, will report 12 questions that assess the information, communication, support and grief interventions (Table 3). The assessment will be on a Likert scale for the first three questions. All other questions will be explored with a Yes/No answer. The satisfactory questionnaire (Fami-Life) evaluating the last moments of life will be given in the last position because it may require more listening time. If we cannot reach a relative after 5 phone calls, he/she will be considered as lost-to-follow up. Only relatives of patients deceased in palliative care unit will be called.

**Table 3 Tab3:** Questions of the Fami-Life questionnaire

1. Have you been satisfied with the information received in the palliative care service?	
2. Were you satisfied with the support your loved one received?	
3. Were you satisfied with the care that health-care workers offered you?	
4. Have you been warned of the aggravation of your loved one?	
5. Did you meet a doctor at the time of the death?	
6. Were you in the room at the time of the death?	
7. Have you received a letter of condolence from the team?	
Would you have liked to receive one?	
8. Were you offered a follow-up of bereavement?	
9. Since the death of your loved one, are you taking drugs that you did not take before?	
If yes, which drugs?	
10. Are you followed by a psychologist?	
If yes: from the ward, or other	
11. Do you participate in a speaking group with other relatives or relatives in the same situation as you?	
12. Would have you liked to have a follow-up after the death of your loved one?	

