### Sample size justification

Prolonged grief reactions were reported in 24.4% [10] at 8 months, and 25.4% [31], 28.6% [15], 30% [32], and 40% [33] at 6 months. We anticipated an incidence of prolonged grief of 25% 6 months after patient death. Horowitz et al reported that the frequency of grief symptoms declined within 6 to 12 months after the bereavement [34]. Grief reactions decreased as a function of time from death with a steepest decrease from the first month to the sixth month after death, and without any significant decrease from 6 months to 13 months [33, 35]. For the current study, we selected a time period of 6 months after the death. According to the medical knowledge, longitudinal studies of relatives at 6 months usually report a participation rate around 60%. To detect the risk factors associated with a prolonged grief with an odd ratio of 2, an alpha risk of 0.05 and a power of 0.80, we anticipate that 500 decedents and their relatives are necessary (assuming the independence of prolonged grief in the relatives of the same family).

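### The sample size of 500 counts enrolled patients in the Abstract but decedents in the Sample size justification, and the follow-up rule makes these different numbers

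*Protocol article*

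**What the plan says.** The protocol article gives its target twice. In the Abstract (Methods) it is a number enrolled: "We planned to enroll 500 patients and their close relatives assuming a 25% prolonged grief rate and a 6-month follow-up available in 60% of relatives". In the Sample size justification it is a number of deaths: "we anticipate that 500 decedents and their relatives are necessary". The second figure is tied to detecting risk factors "with an odd ratio of 2, an alpha risk of 0.05 and a power of 0.80". Risk factors for prolonged grief are listed under Prespecified secondary outcomes.

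Two further inputs stand in the Sample size justification: "We anticipated an incidence of prolonged grief of 25% 6 months after patient death", and the remark that "longitudinal studies of relatives at 6 months usually report a participation rate around 60" per cent.

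Three rules in the Methods bear on the unit of the 500:

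- Timing of entry (Organization of the study): "Consecutive patients will be approached within the first 48 h after palliative care admission". The Inclusion criteria set the same 48 h limit.
- Who is followed (Organization of the study): "Only relatives of patients deceased in palliative care unit will be called".
- What is recorded (Patient's characteristics): "patient’s status at discharge, and length of stay".

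The Inclusion criteria also allow every relative present to be enrolled, so one patient may bring several relatives. The expected number per patient is not given.

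**The concern.** Enrolment takes place before anyone knows how the stay will end, and follow-up depends on how it ended. A family whose patient goes home or is transferred has been enrolled and can complete the HADS at day 3 to 5, but is never called at 6 months. It counts towards 500 patients enrolled and not towards 500 decedents. The rule limiting calls to deaths in the unit is only needed if some enrolled patients do not die there, and recording status at discharge fits with that.

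The only loss the article allows for is the 60% participation, which describes how many relatives take part at 6 months. Exclusion by rule, before any call is made, is a separate step.

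At stake is whether the stated size is the size the calculation needs. As written, a reader cannot tell whether recruitment is complete at 500 admissions or at 500 deaths in the unit, nor how many assessed relatives the risk-factor analysis is expected to have.

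**Working it through.** **Inputs from the article.** Prolonged grief 25%; odds ratio 2; alpha 0.05; power 0.80; follow-up 60%; target 500.

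**Assumptions needed because the article is silent.** Two-sided test; half of the relatives exposed to the risk factor; 25% read as the rate in the unexposed; one relative per patient unless stated otherwise; share d of enrolled patients who die in the unit.

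**Step 1: reproduce the 500.**

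- Odds in the unexposed: 0.25/0.75 = 0.333. Doubled: 0.667. Rate in the exposed: 0.667/1.667 = 0.40.
- Per group, two proportions, pooled variance under the null, no continuity correction: n = [1.96·√(2·0.325·0.675) + 0.8416·√(0.25·0.75 + 0.40·0.60)]² / 0.15² = (1.298 + 0.550)² / 0.0225 = 151.9, so 152, and 304 in total.
- Inflated for follow-up: 304/0.60 = 507, close to 500.

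On this reading the 40% loss takes up the whole inflation, and nothing is left for patients who leave the unit alive. The 500 then behaves like a count of bereaved families with one relative each, which fits the wording of the Sample size justification rather than that of the Abstract.

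The match is not unique evidence. Reading 25% as the overall rate gives 360 assessed, 360/0.60 = 600, with half exposed, or 388 assessed, 388/0.60 = 647, with 30% exposed. Neither gives 500.

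**Step 2: what 500 enrolled patients deliver.** Decedents = 500·d. Assessed relatives, one per decedent = 500·d·0.60. Power is for 25% against 40% with equal groups. Enrolment needed for 500 decedents = 500/d, rounded up.

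| Assumed d | Decedents | Assessed relatives | Power | Enrolment for 500 decedents |
|---|---|---|---|---|
| 100% | 500 | 300 | 79.5% | 500 |
| 95% | 475 | 285 | 77.4% | 527 |
| 90% | 450 | 270 | 75.2% | 556 |
| 80% | 400 | 240 | 70.1% | 625 |
| 70% | 350 | 210 | 64.3% | 715 |

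**Step 3: can several relatives per patient make this up?** The average number of enrolled relatives per patient needed to reach 304 assessed is 304/(500·d·0.60): 1.07 at d = 95%, 1.13 at 90%, 1.27 at 80% and 1.45 at 70%. This treats relatives of one family as independent, as the Sample size justification does.

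**Step 4: the primary outcome.** As a simple proportion at 25%, the Wald half-width is 1.96·√(0.25·0.75/n): 4.9 percentage points with 300 relatives, 5.2 with 270, 5.5 with 240 and 5.9 with 210. The change is modest.

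**The case against.** The best reply is that the Abstract is shorthand. Patients are admitted for end-of-life issues as judged by the palliative care physician, so nearly all may die in the unit, and the two counts may almost coincide. Status at discharge is a routine field and says nothing about how often patients leave alive. This stands as far as the size goes: the 70% to 95% range is assumed, and the article supports no particular value. It does not remove the mismatch, because the article itself makes follow-up conditional on death in the unit.

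A reader might infer more than the text supports, in four ways:

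- *That families of patients discharged alive are not replaced.* The article says nothing either way on replacement, and a condensed article may leave this to the full protocol. One can say only that no replacement or allowance is described.
- *That enrolment closes at 500 or that sites are told to stop at different points.* Neither section contains a stopping rule or an instruction to sites, and 500 is the total of a multicenter study, not a quota per site.
- *That the primary outcome falls short of its required number.* The article states no required number for the incidence estimate; the 500 is justified by the risk-factor analysis, which is secondary.
- *That the study is underpowered.* The unit of analysis is the relative, all relatives present may join, and the independence remark in the Sample size justification shows that more than one per family was expected. Averages of 1.07 to 1.27 per patient would restore 304 assessed relatives at 95% to 80% dying in the unit.

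The last reply offsets relatives only. More relatives per patient do not create more decedents, and decedents are what the Sample size justification says are necessary.

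**Conclusion.** The point holds as an inconsistency in a figure the study relies on. The same 500 is attached to patients enrolled and to decedents, and the article's own entry and follow-up rules make these equal only if every enrolled patient dies in the unit. The 60% covers participation by relatives and not this exclusion.

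The size cannot be fixed from the article. With one relative per patient, each 10 percentage points of enrolled patients not dying in the unit removes 50 decedents and 30 assessed relatives from the 500 and 300 expected. The power figures in the table apply only under one relative per patient, half exposed and 25% in the unexposed; they show the scale and do not establish a deficit. Whether any power is lost depends on the share dying in the unit and the number of relatives per patient, neither of which is given.

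**What to change.** Use one unit for the 500 in the Abstract and in the Sample size justification. There are two ways:

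1. *Keep 500 enrolled patients.* Restate the Sample size justification with the assumed share dying in the unit, the assumed number of relatives per patient, the expected decedents and assessed relatives, and the resulting power for an odds ratio of 2. This costs wording and one recalculation, and is the cheap option.
2. *Keep 500 decedents.* State in the Abstract that the 500 counts patients who died in the unit, tracked through the discharge status already collected, and give the expected enrolment. This costs somewhat longer recruitment: about 556 to 715 patients if 90% to 70% die in the unit.

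In either case, count patients discharged or transferred alive separately from relatives lost to follow-up, so that the 60% assumption can be checked against the group it describes. The data for this are already collected.

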**Discussion:**

This study will be the first to report the psychological consequences of French relatives after a loss of a loved one in palliative care units. Evaluating relatives’ experiences can provide instrumental insights for means of improving support for relatives and evaluation of bereavement programs.

**Trial registration:**

NCT03748225 registered on 11/19/2018. Recruiting patients.

## Background

Bereavement of a loved one is an existential condition during which most people adequately adjust their emotions. However, in some cases, relatives can experience a psychological syndrome with various components such as symptoms of anxiety and depression, of post-traumatic stress-disorder (PTSD), of complicated or prolonged grief disorder (PGD), and increased mortality rates [1]. These conditions associate emotional, behavioral and cognitive symptoms (yearning, searching, detachment, numbness, bitterness, emptiness, and loss of sense and control). Quality of life might be jeopardized. It was initially termed complicated grief, then traumatic grief. In 2013, the classification of mental disorders (DSM-5) proposed to introduce a new diagnostic entity: « Persistent and Complex Bereavement-Related Disorder ». However, some researchers do not recognize it, insisting that evidence justifies the inclusion of PGD, but not complicated grief, as a new mental disorder [2]. The monitoring of bereaved relatives is an integral part of patient care in a patient-family centered care concept. Improving the relatives’ quality of life after a patient’s death is an international priority (Institute of Medicine or World Health Organization) [3–5].

Risk factors of prolonged grief disorders were reported in numerous studies [5–9]. Conflicts between relatives and health-care workers, poor communication and incomplete information during the palliative care stay [9], relatives characteristic’s: age, female gender [8, 10], pessimistic or anxious personality trait [10], financial issues [6], close relation-ship with the deceased patient [7, 10], absence of religiosity [10], and specific social context and family dynamics [11, 12] were reported as risk factors for prolonged grief. Numerous studies worldwide have evaluated post-loss emotional consequences. At 6 and 13 months, at least one psychological consequence was identified in 35.6 and 28.9%, respectively [13]. In Korea, anxiety and depression symptoms were reported for 58 and 57%, respectively [14]. In Australia, PTSD symptoms was diagnosed in 27.6 and 18.3%, respectively [13]. In Portugal, PGD was diagnosed in 28.6 and 15.6%, respectively [15]. In France, numerous studies are focused on population faced to end-of-life situations for intensive care patients [9, 16, 17]. Surprisingly, very few studies are available on relatives of palliative care patients. A French study reported depression in 25% of cancer patient’s spouses after a loss [18].

No data exists on the psychological experience of relatives having a relative hospitalized in palliative care or the incidence of prolonged grief in France. No specific recommendations are available for supporting grieving relatives.

Therefore, the focus of the study will be on prolonged grief reactions in relatives around 6 months after patient’s death in palliative care units. The methodology includes quantitative and qualitative data to better understand the complex, unique and intimate phenomena of grief and to identify needs for support.

## Methods

### Study design

The Fami-Life study is a prospective observational multicenter mixed study to assess the psychological consequences of a loss of a loved one in palliative care units. We designed a quantitative study to assess the psychological consequences of relatives 6 months after patients’ death and a qualitative study to examine the prolonged grieving process. The study timeline and schedule of enrollment, interventions and assessments are presented in Table 1.

**Table 1 Tab1:** Study timeline, schedule of enrollment, intervention and assessments

	Enrollment		Follow-up		
Time points	Within 48 h after Palliative unit admission		Between day 3 and 5 after palliative unit admission	At 6 months	Between 6-months and 1-year
Enrollment					
Eligibility screen	X				
Inform consent	X				
Inclusion	X				
Assessment					
HADS of relatives			X		
(random order)					
IES-R of relatives				X	
HADS relatives				X	
ICG				X	
FAMI-LIFE questionnaire				X	
Qualitative study (interview of relatives with ICG > 25)					X

#### Recruitment of patients and relatives

##### Inclusion criteria

All the inclusion criteria must be fullfilled within 48 h after patient admission:

Patients with a neoplasia should be hospitalized more than 72 h for end-of-life issues. End of life issues are assessed after the first evaluation by the palliative care physician.

Relatives are susceptible to visit the patient during their stay. Relatives are defined as spouse, partner, children, siblings, parents and cousins and any relatives with a strong attachment link. The study will be proposed to relatives present during the first meeting and within 48 h after patient admission. All relatives present can be included because the patient’s death affects the entire group of relatives and not a single individual.

##### Non inclusion criteria

Patients under any form of legal guardianshipPatients with less than 72 h of life-expectancyPatients or relatives who refused the studyPatients or relatives included in a study using the same questionnairesPatients without relatives visiting them within the first 48 h after admissionPatients not hospitalized for end-of-life issuesRelatives not fluent in FrenchDeaf or mute relatives

#### Data collection

##### Center characteristics

All data will be collected on an e-CRF built by the ICUREsearch company (Contract Research Organization). Data will be on center, patients and relatives. Palliative care unit characteristics are the following: hospital type (university, community, or private hospital) number of palliative care beds, number of senior physicians and fellows, physician-to-patient ratio, nurse-to-patient ratio (day and night), presence of a waiting room and relative room, availability of a psychologist, physiotherapist, social worker, occupational and music therapist, biographer; availability of interpret or religious services; availability of a dedicated nurse for relative meetings, of volunteers, of speaking group for relatives; time intervals allowed for visit; organization of different meetings (admission, weekly, death period), delivery of an information leaflet at admission and after death, delivery of a children leaflet, delivery of a condolence letter, bereavement follow-up process, availability of a 24-h visitation policy, age for children visitation, possibility for a pet to visit the patient, availability of staying during the night (bed in the patient ‘room, dedicated room, other), and participation in patient care.

##### Patient’s characteristics

The following data will be collected: demographic characteristics, diagnosis and localization of the neoplasia, presence of metastases, diagnosis of comorbid conditions, symptoms present on admission, presence of advances directives and of a surrogate, patient’s status at discharge, and length of stay. Request of euthanasia at admission or during the stay by patient and use of a continuous sedation until death will be collected.

##### Relatives’ characteristics

The following data will be collected: demographic characteristics, relationship with the patient, educational level, professional occupancy, whether they already have a next one previously hospitalized in a palliative care unit, whether they are the surrogate of the patient, and the presence of health workers at home before admission (nurse, nursing-assistant or occupational worker). The use of “hospital at home” services will also be collected. Request of euthanasia at admission and during the stay by relatives will be collected.

#### Organization of the study

In each center, a local team (physician and nurse or psychologist) will conduct the study. Consecutive patients will be approached within the first 48 h after palliative care admission. Examination of eligibility, its confirmation and inclusion will be performed by the local team. If the relative agrees, the patient will be invited to participate in the study giving permission of using his/her baseline medical information. After inclusion, between day 3 and day 5 after patient admission, a HADS questionnaire [19] will be administered to each relative included in the study.

At 6 months after the patient’s death, the psychologist will call the included relatives to fulfil the questionnaires in a random order (HADS [19], PTSD [20], IGC [21, 22]. The Fami-Life questionnaire, specifically built for the study, will report 12 questions that assess the information, communication, support and grief interventions (Table 3). The assessment will be on a Likert scale for the first three questions. All other questions will be explored with a Yes/No answer. The satisfactory questionnaire (Fami-Life) evaluating the last moments of life will be given in the last position because it may require more listening time. If we cannot reach a relative after 5 phone calls, he/she will be considered as lost-to-follow up. Only relatives of patients deceased in palliative care unit will be called.

**Table 3 Tab3:** Questions of the Fami-Life questionnaire

1. Have you been satisfied with the information received in the palliative care service?	
2. Were you satisfied with the support your loved one received?	
3. Were you satisfied with the care that health-care workers offered you?	
4. Have you been warned of the aggravation of your loved one?	
5. Did you meet a doctor at the time of the death?	
6. Were you in the room at the time of the death?	
7. Have you received a letter of condolence from the team?	
Would you have liked to receive one?	
8. Were you offered a follow-up of bereavement?	
9. Since the death of your loved one, are you taking drugs that you did not take before?	
If yes, which drugs?	
10. Are you followed by a psychologist?	
If yes: from the ward, or other	
11. Do you participate in a speaking group with other relatives or relatives in the same situation as you?	
12. Would have you liked to have a follow-up after the death of your loved one?	

Between 6 and 12 months, the psychologist will call the relatives previously selected (those with an IGC > 25) for a telephone interview assessing their grieving process.

